### Study design

The SpasT-SCI-T study is a prospective, multicenter observational trial performed in France. The study employs a combination of case-control and cohort designs to address its primary and secondary objectives. The inclusion of patients will officially begin on March 17, 2025 and end on September 20, 2026. A total of 40 participants are recruited, divided into three groups:

1**Group 1 (Healthy Controls):** Ten healthy volunteers provide baseline blood samples for comparison.2**Group 2 (SCI Patients):** Twenty patients with acute traumatic SCI confirmed by imaging and no associated TBI.3**Group 3 (TBI Patients):** Ten patients with acute TBI confirmed by imaging and no associated SCI.

The trial consists of three phases:

1**Inclusion Phase:** Participants are enrolled into one of the three study groups based on predefined eligibility criteria.2**Acute Phase (0–14 days):** This phase focuses on the immediate response to trauma, capturing rapid changes in sodium channel fragment levels during the critical early period. Blood samples are collected within 6 hours post-trauma and at multiple time points (Days 1, 3, 5, 7, and 14) to monitor early biomarker kinetics.3**Late Follow-Up Phase (3 and 6 months):** The late follow-up phase assesses long-term changes in sodium channel fragment levels and their association with recovery trajectories and clinical outcomes, including the onset and severity of spasticity. Blood samples are collected during follow-up consultations at 3 and 6 months post-trauma. A 6-month follow-up was selected as clinical signs of spasticity typically stabilize between 2 and 6 months post-injury, with electrophysiological measures showing minimal change thereafter [38].

The CONSORT diagram in Fig 1 provides details on the timeline for enrollment, interventions, and assessments across the participant groups, while the overall study design is summarized in Fig 2.

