Pregnancy or breastfeeding.Pre-existing neurological disorders, such as multiple sclerosis or Parkinson’s disease.History of psychiatric illness or neurodegenerative conditions.Concurrent severe trauma affecting study participation (e.g., multi-organ failure).Inability to provide consent, and absence of a legally authorized representative.Pre-existing cardiovascular or pulmonary diseases.

Informed consent is obtained from all participants using the model consent form and related documents after verifying their eligibility according to the inclusion and exclusion criteria. Recognizing the urgency of inclusion and the acute medical care context, the consent process is tailored to accommodate the specific needs of SCI and TBI patients. The following procedures ensure compliance with ethical and legal requirements while prioritizing participant autonomy and rights:

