Additional statistical methods will include multivariable linear regression models to adjust for potential confounders, including age, sex, injury severity (ASIA grades A–D for SCI, GCS scores for TBI), and concurrent medications (antispasmodics, analgesics, antiepileptics) as primary factors, as well as additional variables from Table 3 such as comorbidities (diabetes, organ failure), trauma context (type of accident), and biological parameters (hemoglobin, renal clearance) where statistically significant or clinically relevant, informed by prior literature [14,21]. This ensures that observed associations between sodium channel fragment levels and outcomes such as spasticity are robust and not influenced by baseline characteristics. Receiver operating characteristic (ROC) curves will be generated to identify threshold levels of sodium channel fragments that differentiate SCI from TBI or predict spasticity onset. To address missing data, multiple imputation methods will be applied, minimizing bias and preserving the validity of the analyses.

Continuous variables will be expressed as means with standard deviations for normally distributed data or medians with interquartile ranges for non-normally distributed data. Categorical variables will be summarized as frequencies and percentages. For all primary and secondary analyses, a two-tailed p-value < 0.05 will be considered statistically significant. Patients who die before the 3-month follow-up will be excluded from spasticity-related analyses due to insufficient time for spasticity development, but all data collected up to the time of death will be included in secondary analyses, such as demographic characterization and early biomarker levels.

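### The adjusted spasticity models carry 7 to 9 or more predictors on at most 20 SCI patients and adjust for a post-baseline drug class, so they cannot ensure robustness

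*Protocol article*

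**What the plan says.** All of this is in the Protocol article.

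- **Model and core covariates** (Statistical methods). The adjusted analysis is multivariable linear regression. Its core covariate list reads: "including age, sex, injury severity (ASIA grades A–D for SCI, GCS scores for TBI), and concurrent medications (antispasmodics, analgesics, antiepileptics) as primary factors".
- **Further covariates.** Other Table 3 variables may be added, "such as comorbidities (diabetes, organ failure), trauma context (type of accident), and biological parameters (hemoglobin, renal clearance) where statistically significant or clinically relevant".
- **Stated result.** "This ensures that observed associations between sodium channel fragment levels and outcomes such as spasticity are robust and not influenced by baseline characteristics".
- **Numbers available** (Study design). "Twenty patients with acute traumatic SCI confirmed by imaging and no associated TBI"; "Ten patients with acute TBI confirmed by imaging and no associated SCI". The Outcomes section confines the spasticity analysis to SCI patients, and Statistical methods removes patients who die before month 3 from it.
- **When drugs are recorded** (Table 3). Usual treatment at inclusion names antiepileptics but not antispasmodics; the list is open-ended. Antispasmodics appear among the additional treatments at discharge and at 3 and 6 months. Antispastic treatment also appears under the Spasticity heading at those same visits.
- **Unadjusted spasticity analysis** (Statistical methods). Fragment level against the Modified Ashworth Scale (MAS) uses Spearman correlation.
- **Status of the study** (Justification of sample size). It is a pilot with an exploratory aim. The SCI number comes from admission rates, with no power calculation.

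**The concern.** Three features of the text work against the conclusion it draws.

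1. The covariate list is long for the number of patients, so the fragment coefficient would be estimated on few residual degrees of freedom.
2. Extra variables may enter "where statistically significant or clinically relevant". Choosing covariates by significance in a sample this small is unstable, and p-values from the chosen model no longer have their nominal meaning. The plan nevertheless applies the 0.05 threshold to all primary and secondary analyses.
3. One of the "concurrent medications (antispasmodics, analgesics, antiepileptics) as primary factors" is a treatment for the outcome itself. A drug class that is plausibly started because spasticity has appeared is not a baseline confounder. Adjusting for it does not serve the stated aim of removing the influence of baseline characteristics.

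The relation between fragment level and spasticity is a secondary objective and central to the prognostic case. As written, an adjusted null result could reflect imprecision or adjustment for a consequence of the outcome. An adjusted positive result could owe its p-value to covariate selection. Either would be reported under a sentence that calls it robust.

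**Working it through.** **The plan's own figure.** The only figure to reproduce is the total: 20 + 10 + 10 = 40, which adds up. No power or precision figure lies behind it.

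**Predictor count** (fragment level counted as one predictor, each drug class as one term)

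- SCI, ASIA as one ordered term: fragment 1 + age 1 + sex 1 + ASIA 1 + drugs 3 = 7.
- SCI, ASIA A–D as three indicators: 1 + 1 + 1 + 3 + 3 = 9.
- SCI with diabetes, organ failure, accident type, hemoglobin and renal clearance at one term each: 9 + 5 = 14. The list is open and accident type may need several terms, so 14 is not a ceiling. Organ failure (heart, lung and kidney in Table 3) would carry little information, because the exclusion "Pre-existing cardiovascular or pulmonary diseases" largely leaves kidney disease.
- TBI, if modelled separately: fragment 1 + age 1 + sex 1 + GCS 1 + drugs 3 = 7; with the five extras, 12.

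**Residual df and precision.** Residual df = n − p − 1. The smallest absolute partial correlation reaching two-sided p < 0.05 is r = t/√(t² + df), with t the 97.5% point on those df. Power is that of the 1-df partial F test, with noncentrality f²(df + 2) and f² = r²/(1 − r²). The partial r of 0.5 is an assumption for illustration; the protocol gives no effect size.

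| Model | n | p | Residual df | Critical partial r | Power at r = 0.5 |
|---|---|---|---|---|---|
| SCI, fragment alone | 20 | 1 | 18 | 0.44 | 69% |
| SCI, fragment + ordered ASIA + age | 20 | 3 | 16 | 0.47 | 63% |
| SCI, primary factors, ASIA ordered | 20 | 7 | 12 | 0.53 | 51% |
| SCI, primary factors, ASIA as indicators | 20 | 9 | 10 | 0.58 | 44% |
| SCI, with five extras | 20 | 14 | 5 | 0.75 | 24% |
| TBI, primary factors | 10 | 7 | 2 | 0.95 | 11% |
| TBI, with five extras | 10 | 12 | −3 | cannot be fitted | – |

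The protocol gives no death rate before month 3. If 2 SCI patients were lost (assumed), the 9- and 14-predictor models would keep 8 and 3 df. If 4 were lost, they would keep 6 and 1.

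**Antispasmodic adjustment.** A simulation of 400,000 patients, with every setting assumed, used a true slope of 0.50 for untreated spasticity on fragment level (both in SD units). The log-odds of treatment were k times true severity, and treatment lowered the observed score by 0, 0.5 or 1 SD. The slopes on the observed score were:

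| k | Unadjusted: effect 0 / 0.5 / 1 SD | Adjusted for treatment |
|---|---|---|
| 1 | 0.50 / 0.45 / 0.40 | 0.43 |
| 2 | 0.50 / 0.43 / 0.35 | 0.35 |
| 4 | 0.50 / 0.41 / 0.32 | 0.27 |

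The effect of adjusting ranges from strong attenuation (0.50 to 0.27, k = 4, no treatment effect) through no change (0.35 and 0.35, k = 2, 1 SD) to a slope slightly nearer the truth (0.40 to 0.43, k = 1, 1 SD). The reason is that treatment also lowers the observed MAS, so leaving it out does not recover the true slope either. The documents fix none of these settings.

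**The case against.** These are additional methods in a pilot study. The primary comparison is ANOVA or Kruskal-Wallis, and the named spasticity analysis is Spearman correlation. Neither depends on the adjusted models. This stands, and it limits the consequences. It does not rescue a sentence asserting that adjustment secures robustness.

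Several stronger readings are tempting but not supported:

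- **That the fragment association would be mostly overfit.** With no true association, expected R² is p/(n − 1), for example 9/19 = 0.47. That describes the whole model. In a prespecified linear model the fragment coefficient is not biased by the number of covariates, and a simulation with 9 predictors on 20 patients rejected a true null 4.7% of the time. The cost is precision. Unreliable p-values come from significance-based entry.
- **That antispasmodic adjustment biases the association towards zero by a known amount.** The simulated range above shows otherwise.
- **That MAS is put into a linear model.** The text names linear models and spasticity as an outcome but does not state the dependent variable. Fragment level as the response is a possible reading.
- **That a TBI model with 7 predictors on 10 patients is planned.** No separate TBI model is stated. It is inferred from the group-specific severity scales, and it would not concern spasticity.
- **That 14 predictors are required.** The extras are conditional, and the coding of ASIA grade is not fixed.

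**Conclusion.** The point holds in a limited form. The protocol's assurance of robustness is not supported by the models it describes. On the most lenient count they put 7 predictors on at most 20 SCI patients (12 residual df). With ASIA as indicators it is 9 (10 df), and with all named extras 14 or more (5 df or fewer). At an assumed partial correlation of 0.5, power falls from 69% for the fragment level alone to 51%, 44% and 24%. A TBI analogue, if fitted, would have 2 residual df and could not take all the extras.

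Allowing entry by significance makes the reported p-values unreliable. Antispasmodics are post-baseline on the Table 3 schedule and plausibly follow from spasticity, so they do not belong among baseline confounders. The direction of the problem is clear but its size is not determined by the documents.

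The df follow from the stated group sizes and covariates under the coding shown. The power figures and simulated slopes rest on assumptions.

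**What to change.** In Statistical methods:

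1. For the SCI spasticity model, prespecify the fragment level plus one or two baseline covariates: ASIA grade as an ordered score, and age. With both, 20 − 3 − 1 = 16 residual df remain. State the dependent variable. If it is MAS, use an ordinal or rank-based method, in line with the planned Spearman analysis.
2. Limit any TBI model to at most one covariate (GCS).
3. Remove entry of covariates by statistical significance.
4. Take antispasmodics out of the adjustment set for spasticity, and use the recorded antispastic treatment in a sensitivity analysis only.
5. Delete the sentence claiming that adjustment ensures robust associations, and label the adjusted models exploratory.

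The cost is a change of wording. The downside is that fewer variables are adjusted for, so some residual confounding remains and should be acknowledged when results are reported.

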## Introduction

Spinal cord injury (SCI) is a tragic condition with lifelong physical, psychological, and economic consequences, affecting millions of individuals worldwide [1–3]. Accurate and timely assessment of its severity is paramount for predicting outcomes and guiding therapeutic interventions. However, current diagnostic methods, which rely primarily on clinical examinations and imaging, lack the sensitivity required for precise evaluation, especially during the critical acute phase [4–6]. This diagnostic gap underscores the urgent need for novel, reliable biomarkers to improve clinical decision-making.

One of the most prevalent and disabling complications of SCI is spasticity, which affects up to 75% of patients within the first year post-injury [7,8]. Spasticity, classically defined as hypertonia with a velocity-dependent increase in stretch reflexes [9], encompasses a spectrum of clinical manifestations, including clonus, exaggerated reflexes, muscle spasms, and involuntary leg crossing [10,11]. These symptoms severely disrupt daily activities, quality of life, and rehabilitation efforts. Without early and effective management, spasticity progresses to complications such as muscle shortening, joint contractures, and painful pressure sores [12,13]. The unpredictable onset and variable severity of spasticity, ranging from mild stiffness to severe, uncontrollable spasms, pose significant challenges for clinicians, emphasizing the urgent need for reliable predictive biomarkers [14,15].

Advances in our understanding of spasticity pathophysiology have highlighted promising targets for biomarker discovery [16,17]. Secondary injury processes in SCI trigger molecular cascades, including excessive glutamate release, intracellular calcium overload, and calpain activation [18,19]. Calpains, calcium-activated proteases, cleave Nav1.6 voltage-gated sodium channels [20–22], which are predominantly expressed in spinal motoneurons [23–25]. This proteolysis disrupts the normal inactivation of Nav1.6 channels, leading to an upregulation of persistent sodium currents (I_NaP_) [20–22]. The pathological I_NaP_ drives motoneuron hyperexcitability and sustained depolarizations (plateau potentials), directly contributing to spasticity in both animals [26–31] and humans [32–34].

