The identification of sodium channel fragments as products of calpain-mediated cleavage offers a novel biomarker opportunity, linking the molecular pathology of SCI to clinical outcomes. These fragments hold potential not only for assessing SCI severity but also for predicting the onset and magnitude of spasticity [21]. Notably, similar sodium channel cleavage mechanisms have been observed in traumatic brain injury (TBI), suggesting broader applicability of these biomarkers across central nervous system (CNS) injuries [35–37].

The focus on SCI and TBI in this study is thus driven by their shared traumatic etiology and the established role of calpain-mediated sodium channel cleavage in their pathophysiology. SCI, with its high prevalence of spasticity (up to 75% of patients), and TBI, a leading cause of CNS trauma, both exhibit this molecular signature in preclinical models [21,35–37], distinguishing them from non-traumatic CNS conditions such as stroke or neurodegenerative diseases, where this mechanism is not documented. By targeting these traumatic injuries, we aim to leverage this specific biomarker to address the unmet diagnostic and prognostic needs in acute CNS trauma management.

The present *SpasT-SCI-T* clinical trial protocol aims to evaluate calpain-mediated sodium channel fragments as diagnostic biomarkers for SCI and TBI and as prognostic markers for spasticity. By bridging molecular mechanisms and clinical outcomes, this study seeks to advance the management of CNS injuries and spasticity, paving the way for more accurate diagnoses, enhanced prognostic precision, and personalized therapeutic strategies.

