### Justification of sample size

The study includes a total of 40 participants distributed as follows: 20 patients with spinal cord injury (SCI), 10 patients with traumatic brain injury (TBI), and 10 healthy controls. The selection of 20 SCI patients is based on the annual admission rates for SCI at the study institution, ensuring a representative sample of the population served. The inclusion of 10 TBI patients is justified to account for potential confounding factors arising from the overlapping but distinct injury mechanisms of SCI and TBI. Furthermore, 10 healthy controls are included to provide a robust baseline for sodium channel fragment levels, facilitating a balanced comparison across the three groups.

This sample size is sufficient to detect meaningful trends and associations between sodium channel fragments and clinical outcomes, including spasticity, while maintaining feasibility within the scope of a pilot study. The findings will generate preliminary evidence regarding the diagnostic and prognostic utility of sodium channel fragments in neurological injuries and will guide the design of larger-scale clinical trials.

Given the exploratory nature of this study, no formal interim analyses are planned. As the trial involves minimal-risk procedures, such as blood sampling, no pre-specified stopping rules have been established. In the event of significant deviations from the protocol or unforeseen safety concerns, the trial steering committee will consult the Ethics Committee to determine whether adjustments or study termination are necessary. All such decisions will be transparently documented and communicated to relevant stakeholders, including regulatory authorities, to ensure compliance with ethical standards.

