### Statistical methods

The primary objective of this study is to quantify sodium channel fragments in blood samples and compare their levels across the three participant groups: healthy controls (Group 1), SCI patients (Group 2) and TBI patients (Group 3). To address this objective, statistical analyses will begin with group comparisons.

1**Group Comparisons:** For normally distributed data, one-way analysis of variance (ANOVA) will be employed to identify differences in sodium channel fragment levels among the three groups. If data are not normally distributed, the Kruskal-Wallis test will be applied as a non-parametric alternative. Post-hoc analyses will follow these tests to assess pairwise comparisons, using Tukey’s test for ANOVA or the Mann-Whitney U test for non-parametric data.2**Effect Size Calculation:** Effect sizes (e.g. Cohen’s d for t-tests or η² for ANOVA) will be calculated to quantify the magnitude of differences between groups.

For secondary outcomes, analyses will focus on the temporal kinetics of sodium channel fragments and their correlation with clinical outcomes.

1**Temporal Kinetics:** Changes in fragment levels over time, measured at baseline (6 hours), during the acute phase (Days 1, 3, 5, 7), and at follow-up (Months 3 and 6), will be analyzed using repeated-measures ANOVA for normally distributed data. For non-normally distributed data, the Friedman test will be used. Bonferroni corrections will be applied during multiple comparisons.2**Spasticity Correlation:** The relationship between sodium channel fragment levels and spasticity severity in SCI patients will be assessed using Spearman’s rank correlation coefficients, with spasticity evaluated at Months 3 and 6 using the Modified Ashworth Scale (MAS).3**Subgroup Analysis (SCI Severity):** Subgroup analyses will investigate whether sodium channel fragment levels differ by injury severity. In SCI patients, severity will be categorized based on the American Spinal Injury Association (ASIA) Impairment Scale grades (A–D). Similarly, spasticity onset will be analyzed as a binary outcome (presence vs. absence). For TBI patients, the Glasgow Coma Scale (GCS) will be used to classify injury severity, enabling comparisons of sodium channel fragment levels across defined severity subgroups.

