### Strengths and limitations

This study uniquely explores sodium channel fragments, providing an innovative and specific biomarker linked directly to calpain-mediated pathophysiology common to SCI and TBI. Unlike previous biomarkers, sodium channel fragments offer neuronal specificity, sustained temporal expression suitable for both acute and chronic phases, and potential for wide applicability in traumatic CNS conditions. Despite their promise, challenges remain before clinical adoption. Patient factors like demographics and comorbidities may affect fragment levels, requiring larger studies to define normative ranges and thresholds. Standardized sample processing is also essential for reproducibility. Integrating biomarker analysis into clinical workflows demands infrastructure and validation efforts.

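### Fragment thresholds taken from ROC curves in 20 vs 10 and at most 20 patients will carry optimistic sensitivity and specificity unless corrected, and the analysis section does not mark them as exploratory

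*Protocol article*

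**What the plan says.** Under Statistical methods, after the regression models, the protocol article states that ROC "curves will be generated to identify threshold levels of sodium channel fragments that differentiate SCI from TBI or predict spasticity onset". Finding a cut-off is therefore the declared purpose of these curves. The sentence does not name the blood draw, the direction of the marker or the rule for choosing the cut-off.

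The patients available are given under Justification of sample size: "20 patients with spinal cord injury (SCI), 10 patients with traumatic brain injury (TBI), and 10 healthy controls". For spasticity only the SCI group counts, and it can shrink: "Patients who die before the 3-month follow-up will be excluded from spasticity-related analyses". Spasticity onset is handled as present or absent. The Introduction says that spasticity "affects up to 75% of patients within the first year post-injury". Study design lists eight draws per injured patient: within 6 hours, Days 1, 3, 5, 7 and 14, and Months 3 and 6.

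Two other places bear on how a threshold should be read. Justification of sample size presents the study as a pilot that yields preliminary evidence for larger trials. Strengths and limitations says that patient factors may affect fragment levels, "requiring larger studies to define normative ranges and thresholds".

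**The concern.** When a cut-off is chosen because it separates the patients at hand best, its sensitivity and specificity in those same patients exceed what it will achieve in new ones. The excess grows as the smaller group shrinks. Here the smaller group is 10 in one comparison and may be about 5 in the other. Choosing the marker's direction or the best of several draws from the same data adds to it.

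The article gives no other source of patients, so any accuracy quoted for a threshold would come from these 20 to 30 people. A reader planning the larger study that the pilot is meant to guide could take such a figure at face value. The sentence that sets the aim also carries no exploratory label, although the rest of the article supplies grounds for one.

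**Working it through.** **There is no figure to reproduce.** The article gives no target AUC, precision or power for the ROC analysis. The counts 20 + 10 + 10 = 40 agree with the stated total.

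**Inputs from the article.**
- SCI vs TBI: 20 vs 10.
- Spasticity: at most 20 patients. At the upper rate of 75%, 0.75 × 20 = 15 with and 5 without. Because 75% is a ceiling and a first-year figure, while follow-up here ends at 6 months, a 10 vs 10 split is shown as well.
- Draws: 1 + 5 + 2 = 8.

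**Assumptions.** The marker is normally distributed. The cut-off maximises the Youden index J = sensitivity + specificity − 1. J is then read off the same patients. Direction is either fixed beforehand or chosen from the data.

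**Step 1: a marker of no value (true J = 0).** Mean apparent J by simulation, 95th percentile in brackets (10,000 runs; 1,000 for 200 vs 100):

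| Comparison | Direction fixed | Direction from data |
|---|---|---|
| 20 vs 10 (SCI vs TBI) | 0.21 (0.45) | 0.31 (0.50) |
| 10 vs 10 (spasticity, balanced) | 0.23 (0.50) | 0.34 (0.60) |
| 15 vs 5 (spasticity at 75%) | 0.27 (0.60) | 0.40 (0.67) |
| 12 vs 4 (four patients lost) | 0.30 (0.67) | 0.44 (0.67) |
| 200 vs 100 (for contrast) | 0.07 (0.15) | 0.10 (0.16) |

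At 15 vs 5, J reaches 0.5 or more in about 10% of studies with direction fixed and about 20% with direction free. At 20 vs 10 the shares are 3% and 6%.

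**Step 2: picking the draw as well.** With the best of eight draws chosen, an assumed within-patient correlation of 0.5 and direction free (3,000 runs), the null J averages 0.45 (20 vs 10) and 0.58 (15 vs 5). With only the six draws up to Day 14 it is 0.43 and 0.56.

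**Step 3: a marker with some value.** For a true AUC of 0.70, the distance between group means is δ = √2 × 0.524 = 0.742 SD. The best attainable J is 2Φ(δ/2) − 1 = 2Φ(0.371) − 1 = 0.29. With direction fixed (8,000 runs):
- 20 vs 10: apparent J 0.44, truly delivered 0.25.
- 15 vs 5: apparent J 0.49, truly delivered 0.25, so about double.

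**Step 4: the AUC.** With direction and draw fixed, the mean null AUC is 0.50, so it is unbiased. It is imprecise. The Hanley-McNeil variance is [A(1−A) + (n₁−1)(Q₁−A²) + (n₀−1)(Q₂−A²)] / (n₁n₀), with Q₁ = A/(2−A) and Q₂ = 2A²/(1+A). At A = 0.70, Q₁ = 0.538 and Q₂ = 0.576.
- 15 vs 5: (0.210 + 14 × 0.0485 + 4 × 0.0865)/75 = 0.0165, SE 0.128, 95% half-width 0.25.
- 20 vs 10: (0.210 + 19 × 0.0485 + 9 × 0.0865)/200 = 0.0095, SE 0.098, 95% half-width 0.19.

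**Step 5: does a correction work?** With the cut-off re-chosen inside leave-one-out cross-validation (direction fixed, 1,000 runs), the null J falls to about 0.00 (20 vs 10) and 0.01 (15 vs 5). The optimism goes, but the imprecision stays: a specificity of 4/5 has an exact 95% CI of 28% to 99%, and 8/10 one of 44% to 97%.

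**The case against.** The strongest reply is that the article devotes one sentence to ROC curves and leaves the detail to an analysis plan that is not shown. It promises no sensitivity or specificity and does not say that accuracy will be scored uncorrected on the same patients. That stands as far as it goes. A reader might infer that uncorrected scoring is planned, but the text does not say so, and silence about internal validation would not by itself be a finding. What remains is the stated aim of deriving thresholds from these patients. Others information also presents the article as describing the methodology in full. An unseen plan could add a correction without changing that aim.

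A reader might also infer that the article contradicts itself on thresholds. It does not. Candidate cut-offs from a pilot, followed by definitive ones from larger studies, form a reasonable sequence. The tension is that Statistical methods does not say the thresholds are candidates, while Conclusions speaks of establishing the fragments as robust biomarkers.

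The size of the optimism also depends on the scenario. The 15 vs 5 split uses the highest spasticity rate. The article's mechanism gives spasticity an expected direction, so the fixed-direction values fit that comparison best. The Youden rule is an assumption. These points lower the figure but do not remove it: the smallest null value in either planned comparison is still 0.21.

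Finally, one might argue that the diagnostic curve should contrast injured with healthy people. The article's aim, "to evaluate calpain-mediated sodium channel fragments as diagnostic biomarkers for SCI and TBI and as prognostic markers for spasticity", does not prescribe that contrast. The primary three-group comparison already sets the injured groups against controls, so this is a preference and is not raised here.

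**Conclusion.** The point holds in a limited form. Run as written, with no correction added, sensitivity and specificity at a chosen threshold would be optimistic. For a useless marker the mean apparent Youden index would be about 0.2 to 0.3 with direction fixed and 0.3 to 0.4 with direction chosen from the data. For a marker with a true AUC of 0.70 at 15 vs 5, apparent performance would be about twice what is delivered. This rests on a normal marker, the Youden criterion and the group sizes above; the figures for multiple draws also rest on the assumed correlation of 0.5.

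It would go too far to conclude that ROC analysis here must make a useless marker look discriminating. With direction and draw set beforehand the AUC is unbiased, and the optimism lies in the accuracy at the maximised cut-off. Nor do the documents support a ban on showing any threshold. ROC curves are an additional analysis, so the primary comparison is unaffected.

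**What to change.** In Statistical methods, or in the analysis plan if it is still open:

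- Name one blood draw and one marker direction for each ROC comparison before fragment data are linked to outcomes.
- Make the AUC with its 95% CI the main ROC result.
- Report sensitivity and specificity at any cut-off only with bootstrap or cross-validated optimism correction, repeating the whole choice of cut-off in each resample, and with confidence intervals.
- Call the thresholds exploratory, in line with Justification of sample size and Strengths and limitations.

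The cost is a few sentences, a little more analysis work and less favourable published accuracy figures. No additional patients or samples are needed. The correction removes the bias but not the wide intervals, which follow from the sample size.
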